Appendix 1: Step-by-step field procedures

Appendix 2: Flow chart for the work in the field site

## 1. OBJECTIVE

To compare the efficacy of oral albendazole (single 400-mg dose) and oral mebendazole (single 500-mg dose) against hookworm infection among schoolchildren in central Lao PDR.

Low efficacies of mebendazole against hookworm infections have been reported from Mali, Tanzania and Vietnam (De Clercq et al., 1997, Albonico et al., 2003; Flohr et al. 2007). Albendazole, on the other hand, resulted in high cure rates against hookworm infections (for a review see: Horton, 2000). In view of the low cure rates obtained with mebendazole against hookworm infections, there is a pressing need to conduct well-designed trials that provide new data regarding the efficacy of commonly used anthelmintics against hookworm infections in different settings, so that the most efficacious drugs can be used in control programmes.

### 3. HYPOTHESES

Mebendazole (MBZ) 500-mg, single oral dose, has a significantly inferior efficacy to cure (complete clearance,  $\pi$ ) and reduce intensity of infection (mean eggs per gram [epg] stool) rate for treatment of hookworm infections compared with albendazole (ABZ) 400-mg, single oral dose:

$H_0 = \phi \text{ MBZ} - \phi \text{ ABZ} > \delta$ ; and

$H_a = \phi \text{ MBZ} - \phi \text{ ABZ} < \delta$  ( $\delta$  is the minimum difference of clinical significance)

### 4. METHODS

**4.1 Study design:** Randomized, controlled trial in schoolchildren.

**4.2 Intervention:** Children will be randomly assigned to receive either MBZ 500-mg (Group A) or ABZ 400-mg (Group B). Drugs will be administered at a single oral dose.

#### 4.3 Primary outcome measures

1. Hookworm parasite clearance (no egg excretion of initially hookworm-positive children after treatment), assessed 21-23 days post-treatment.
2. Hookworm egg reduction rate (reduction of hookworm intensity, measured in epg) 21-23 days post-treatment.

#### 4.4 Study area and population

1. One selected primary school in a village with a known high prevalence of hookworm among schoolchildren ( $\geq 50\%$ ) in Batieng district, Champasack province, in southern Lao PDR.
2. Schoolchildren, aged 5-16 years, who appear healthy upon a general clinical check, will be eligible.

#### 4.5 Time schedule

1. Baseline screening (from 28nd to 4th May 2008): From each child two stool samples will be collected within 2-3 days and examined with the Kato-Katz method (Katz et al., 1972). Two Kato-Katz thick smears will be prepared from each stool sample. Hookworm-positive children (at least 1 hookworm egg in one of the four Kato-Katz thick smears) will be treated.

2. End-of-study screening (from 27th to 30th May 2008; 21-23 days post-treatment): From each child, 2 stool samples will be obtained within 2-3 days and duplicate Kato-Katz thick smears will be examined as before.

#### **4.6 Sample size**

In a recent meta-analysis carried out at the Swiss Tropical Institute on the efficacy of the 4 anthelmintics that are on the WHO model list of essential drugs, the efficacy (parasite clearance rates, cure rate) of MBZ (500-mg single dose) and ABZ (400-mg single dose) was estimated at 15% (6 randomized, placebo-controlled trials, range 8-91%) and 75% (14 randomized, placebo controlled trials; range 45-100%), respectively (Keiser & Utzinger, 2008). The efficacy of mebendazole varied largely. In order to account for this variation (uncertainty) we tripled the mean efficacy for the sample size calculations (51% instead of 15%). The estimated ALB efficacy of 75% was compared with 51% for MBZ. With a 90% power, and an alpha error of 5%, we calculated a sample of 85 children per treatment group. (Calculation assumes superiority of ABZ: 1- tailed test, Table 1). In total 170 children are required. Given a drop-out rate of 10% we need to enroll 190 children with a hookworm infection. Assuming a hookworm prevalence of 50% in the study area, approximately 400 children will need to be screened to identify the required number of study participants. Taking into account that from each individual 2 stool samples will be examined 800 stool samples will need to be examined in the base-line survey resulting in 1,600 Kato-Katz thick smears. In the follow-up examination 21-23 days after treatment, only the treated children (i.e. n=200) will be examined resulting in 400 stool samples and 800 Kato-Katz thick smears. In the entire study 1,200 stool samples will be collected and 2,400 Kato-Katz slides examined.

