4.8.1.3. Measurements (see Figure 1)

4.8.1.4. Randomization of subjects into 2 equal arms

4.8.1.5. Group A; single oral dose of MBZ (500-mg). Group B: single oral dose of ABZ (400-mg).

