#### **4.9 Analysis**

All data will be double-entered into EpiData (version 3.1 Denmark). The differences between groups will be analyzed by using the Pearson  $\chi^2$  test.

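### The stated basis (75% vs 51%, 90% power, 1-tailed 5%) gives about 68 children per arm, not 85; the power basis is misstated, though the trial is not undersized

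*Protocol*

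**What the plan says.** Section 4.6 of the protocol sets out the calculation for the cure-rate comparison. The rates are given as "The estimated ALB efficacy of 75% was compared with 51% for MBZ". The error rates and result are: "With a 90% power, and an alpha error of 5%, we calculated a sample of 85 children per treatment group". The direction is given in brackets: "Calculation assumes superiority of ABZ: 1- tailed test, Table 1". The total follows: "In total 170 children are required". A 10% drop-out allowance is then added, giving 190 to enrol. Section 4.8.1.4 specifies equal allocation: "Randomization of subjects into 2 equal arms".

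Section 4.9 gives the analysis in one sentence: "The differences between groups will be analyzed by using the Pearson" chi-square test. It states no sidedness, significance level or continuity correction. Section 3 words the hypothesis directionally, with mebendazole (MBZ) inferior to albendazole (ABZ), and uses a minimum difference δ to which it gives no value.

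**The concern.** Section 4.6 states every input of a standard two-proportion calculation, so the result can be checked, and 85 is 25% above what those inputs give (85/68 = 1.25). A gap of that size is not rounding.

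The trial's size is not at risk. What is at stake is the error rate attached to cure, the first of the two primary outcomes in Section 4.3. Sections 3 and 4.6 point to a one-sided 5% test in favour of ABZ. Section 4.9 names a test that in its usual form is two-sided, which at 5% allows 2.5% in that direction. A result favouring ABZ with a two-sided p between 0.05 and 0.10 would be significant on the first reading and not on the second. That should be settled before the data are seen. The cure-rate ranges cited in Section 4.6 overlap (8-91% for MBZ, 45-100% for ABZ), so the plan should also say how a result in the other direction would be read.

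**Working it through.** **Inputs.** From Section 4.6: p₁ = 0.51 (MBZ), p₂ = 0.75 (ABZ), difference d = 0.24, mean p̄ = 0.63, power 90% (z = 1.2816), alpha 5% 1-tailed (z = 1.6449; a two-sided test uses 1.9600). From Section 4.8.1.4: equal arms. The null value is taken as zero difference, because the protocol gives no number for δ.

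**Variance terms.** 2p̄(1−p̄) = 2 × 0.63 × 0.37 = 0.4662, square root 0.6828. p₁(1−p₁) + p₂(1−p₂) = 0.2499 + 0.1875 = 0.4374, square root 0.6614. d² = 0.0576.

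**Attempt to reproduce 85 on the stated basis (one-sided 5%, 90% power).**
- Pooled variance under the null, unpooled under the alternative: n = (z_α√[2p̄(1−p̄)] + z_β√[p₁(1−p₁)+p₂(1−p₂)])² / d² = (1.1231 + 0.8476)² / 0.0576 = 67.4, so 68.
- Unpooled throughout: (1.6449 + 1.2816)² × 0.4374 / 0.0576 = 65.03, so 66.
- Pooled throughout: 8.564 × 0.4662 / 0.0576 = 69.3, so 70.
- Arcsine: 67.5, so 68.
- Continuity-corrected, (n/4)(1 + √[1 + 4/(nd)])² with n = 67.4: 75.5, so 76.
- Exact one-sided Fisher test: about 75.

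No one-sided version exceeds 76, so 85 is not reproduced.

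**Which settings do give about 85?**
- Two-sided 5%, 90% power: (1.3382 + 0.8476)² / 0.0576 = 82.9. With the pooled-throughout formula: 10.507 × 0.4662 / 0.0576 = 85.04.
- One-sided 5%, 95% power: (1.1231 + 1.0878)² / 0.0576 = 84.9.

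The text does not show which was used.

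**Other explanations tried.**
- Drop-out: 76/0.9 = 84.4, so 85. But Section 4.6 adds drop-out after the 85 (170/0.9 = 189, in line with 190), so it would be counted twice.
- The MBZ rate: Section 4.6 says "we tripled the mean efficacy for the sample size calculations (51% instead of 15" per cent), but 3 × 15% = 45%. At 45% vs 75% the size is 44 per arm one-sided or 54 two-sided, further from 85. The 45/51 discrepancy needs its own correction; here 51% is taken as stated.

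**Power of the uncorrected chi-square, by enumerating both binomial distributions.**

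| Per arm | One-sided 5% | Two-sided 5% |
|---|---|---|
| 68 | 89.9% | 83.6% |
| 83 | 94.4% | 89.9% |
| 85 | 94.9% | 90.5% |

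By normal approximation, a continuity-corrected two-sided test at 85 per arm has 87.7% power, so whether the correction is applied matters to the 90% claim.

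**The case against.** The case on the other side has four parts.

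*The promised power is delivered.* With the uncorrected test, 85 per arm gives at least 90% power on either reading, and no enrolment figure changes. This stands. A reader might infer from the failed arithmetic that the trial is undersized, or that it should be cut to 68. The figures support neither: 85 is above the stated one-sided requirement, and 68 would leave 83.6% two-sided power.

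*The basis may lie elsewhere.* Section 4.6 cites a Table 1 that is not in the text at hand, and Section 3 tests against a margin δ. A one-tailed test against a margin of 3 percentage points with unpooled variance gives 8.564 × 0.4374 / 0.21² = 84.9. So 68 is the answer for a zero null difference, not for every conceivable null. But δ has no value in the protocol and Section 4.6 mentions no margin. The inputs that Section 4.6 does state still do not yield its result. Nothing is inferred from the absence of the table.

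*Pearson's chi-square is not necessarily two-sided.* In a 2×2 table the statistic is the square of z, so a directional decision can be taken from it, and the threshold may be set in an analysis plan that is not shown. This is right as far as it goes. A reader might infer that the analysis definitely uses a different error rate from the sample size, or that the 1-tailed wording was meant to allow a later claim of significance. Section 4.9 states no sidedness, so neither is documented. What remains is that a test named without a one-sided version is normally read as two-sided, while Sections 3 and 4.6 are directional.

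*A pre-stated one-sided test is legitimate.* Agreed. If that was the intention, the 90% is what needs correcting, and the fix allows for it.

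**Conclusion.** The concern holds as a misstated power basis. On the inputs in Section 4.6, with a zero null difference, about 68 children per arm are needed (66 to 70 by the uncorrected formulas, 76 with continuity correction) against the stated 85. Either the 1-tailed description or the 90% is then wrong as written. A two-sided test at 90% power and a one-sided test at 95% power both fit 85, and the document does not settle which was meant.

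The consequence is limited. Assuming 75% vs 51% and the uncorrected test, power at 85 per arm is 94.9% one-sided or 90.5% two-sided. The substantive gap is that the threshold for the cure comparison is not fixed consistently across Sections 3, 4.6 and 4.9, which leaves the false-positive rate in favour of ABZ at either 5% or 2.5%. This should be fixed before analysis, but it does not threaten the trial's ability to answer its question.

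**What to change.** Preferred wording for Section 4.6: two-sided alpha 5%, Pearson chi-square without continuity correction, cure rates 75% vs 51%; 85 children per arm gives about 90.5% power. Delete the 1-tailed statement. In Section 4.9, say that the test is uncorrected and that significance means two-sided p < 0.05. In Section 3, align the hypotheses: a null of equal cure rates against a two-sided alternative, with δ either removed or given a value and a stated role. Keep 85, 170 and 190.

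If the sponsor did intend a one-sided 5% test, keep that description, state the power at 85 per arm as about 95%, and say in Section 4.9 that the test is one-sided in favour of ABZ.

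Neither route changes enrolment. The preferred route is more than a wording change in one respect: the false-positive rate in favour of ABZ falls from 5% to 2.5%, so the threshold is stricter, and power on the stated assumptions is 90.5% instead of 94.9%.

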#### **4.7 Outcome measurements**

##### **4.7.1. Assessment of infection performed by**

1. Kato-Katz thick smears for diagnosis of hookworm (and other soil-transmitted helminth) infection in the field. Minimum acceptable samples of stool on two consecutive days per individual. 2 slides examined per stool (total 4 slides per person). Each Kato-Katz will be established and read within 30 to 45 minutes after establishment. Each parasite species will be recorded, for each species the number of eggs identified will be counted. A person is considered infected if at least one hookworm egg on 1 slide can be detected.
2. Quality control: 10% random selection of KK slides will be read by a second reader (senior microscopists).

#### **4.7.2. Clinical assessment measurements**

- 1) An individual questionnaire will be administered to all the participating children (interviews will be conducted by the head teachers):
  - a. Demographics (i.e. age and sex) and socio-economic indicators (e.g. household assets ownership)
  - b. Perceived morbidity indicators with a recall period of 2 weeks.
  - c. Risk factors for hookworm infection (food, routine lifestyle, contact habit, standard of hygiene etc.)
  - d. Recent medical history / other personal medical history within the last 4 weeks (including anthelmintic treatment)
  - e. Individual side effect questionnaire will be administered
  - f. Anthropometric measurements: height, weight, MUAC,
  - g. Nutritional measurements: hemoglobin level
- 2) Individual adverse effect questionnaire form will be administered to all subjects enrolled within 24 hours following ABZ either MBZ.

#### **4.7.3. Randomization and allocation concealment**

A random numbers table will be used to generate random number sequences for the allocation of the two group treatments, created by a statistician who will not otherwise be involved in the trial.

- i. Group A: single oral dose of MBZ (500-mg). Group B: single oral dose of ABZ (400-mg).
- ii. Numbered containers will be used for allocation concealment.
- iii. The nurse/clinician who will administer the drugs will not be same person as the one who will record the adverse events (masked to the drug treatment).
- iv. The investigators (laboratory personnel, nurse/clinician administering the drugs, nurse/clinician assessing adverse events), will be blinded.
- v. MBZ and ABZ will be ordered by Ministry of Health (MOH) of Lao PDR that currently have been used for mass- treatment
- vi. Drugs will be packaged by a person not otherwise involved in the study in seal opaque envelopes with unique identification numbers provided by the statistician
- vii. On the treatment day, drugs will be given under supervision on an empty stomach 30 minutes before meals
- viii. A blinding
  - a. The principle investigator and patients will see the drugs.
  - b. The laboratory technicians (reading the Kato-Katz thick smears) are blinded.
  - c. The nurse/clinicians who monitor the side effects are blinded.

## **4.8 Study procedures**

The study will be carried out in one primary school in an area of known high hookworm prevalence rates ( $\geq 50\%$ ). In a baseline survey the status of hookworm infection prevalence and intensity will be assessed (other soil-transmitted helminth infections will also be assessed quantitatively). Subsequently, those children with a confirmed hookworm infection (at least 1 hookworm egg in at least one of the four Kato-Katz thick smears) will be randomly allocated either to the MBZ or the ABZ treatment group. Finally, the treatment outcome will be assessed in a follow-up survey 21-23 days after treatment.

### **4.8.1 Base-line procedure (Figure 1)**

#### **4.8.1.1 Inclusion criteria:**

- i. All schoolchildren aged 5-16 years are eligible.
- ii. Infection with hookworms as confirmed by parasitological stool examination (at least 1 hookworm egg in at least one of the four Kato-Katz thick smears)
- iii. Written informed consent of parents and children

#### **4.8.1.2. Exclusion criteria:**

- i. Presence of any abnormal medical condition, judged by the medical doctor. If several patients experience serious adverse events the study will be stopped
- ii. Recent history of anthelmintic drug treatment (albendazole, mebendazole, pyrantel, levamisole within past 4 weeks)
- iii. Attending other clinical trials during the study
- iv. For females: pregnancy or lactation as assessed by the medical doctor last menstrual cycle, upon initial clinical assessment
- v. Children with chronic illness or acutely ill children (any disease).
- vi. known or reported hypersensitivity to albendazole or mebendazole.

4.8.1.2. Information and written informed consent from parents or legal guardians of all subjects enrolled

4.8.1.3. Measurements (see Figure 1)

4.8.1.4. Randomization of subjects into 2 equal arms

4.8.1.5. Group A; single oral dose of MBZ (500-mg). Group B: single oral dose of ABZ (400-mg).

4.8.1.6 Compliance: treatment is under supervision

4.8.1.7 Patients receiving the drugs will be kept for observation for at least 3 hours for any acute adverse events (AEs). If there is any abnormal finding, the study physicians will perform full physical examination on each individual and findings will be recorded.

- 4.8.1.8 AEs within 24 hours of drug administration will be assessed by side effect questionnaire. Those patients who report AEs will be examined carefully by the study physician and, when necessary, action will be taken (see appendix 1).

#### **4.8.3 Follow-up survey (21-23 days after treatment)**

- i. Record the number of absent children and reason to Day 21
- ii. Record the number of withdrawn subject and reason to Day 21
- iii. All individual receiving treatment will be revisited and all base-line measurements will be repeated using same procedures and methods (except hemoglobin concentration will not be done after treatment).
- iv. All infected children will be treated at the end of the trial with PO single dose ABZ 400 mg

#### **4.9 Analysis**

All data will be double-entered into EpiData (version 3.1 Denmark). The differences between groups will be analyzed by using the Pearson  $\chi^2$  test.

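### The cure-rate comparison in 4.9 is a valid but unadjusted chi-square that leaves unused the egg count taken from every child before allocation

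*Protocol*

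**What the plan says.** Section 4.3 lists two primary outcomes. This point concerns the first: "Hookworm parasite clearance (no egg excretion of initially hookworm-positive children after treatment), assessed 21-23 days post-treatment". Section 4.9 is the whole analysis section, and its only inferential statement is "The differences between groups will be analyzed by using the Pearson" chi-square test. It names no model or covariate.

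The protocol collects a baseline measure of intensity. Section 4.8 states that "In a baseline survey the status of hookworm infection prevalence and intensity will be assessed". In section 4.7.1, four slides are read per child and "for each species the number of eggs identified will be counted". Allocation comes afterwards: section 4.8 continues with "Subsequently, those children with a confirmed hookworm infection" being randomised. Sections 4.7.3 and 4.8.1.4 describe a random number sequence and two equal arms, with no stratification by intensity.

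The entry threshold is low: "A person is considered infected if at least one hookworm egg on 1 slide can be detected".

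For sizing, section 4.6 states "The estimated ALB efficacy of 75% was compared with 51% for MBZ" and "With a 90% power, and an alpha error of 5%, we calculated a sample of 85 children per treatment group".

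**The concern.** Entry runs from a single egg upward, and cure means reading zero on the same four-slide scheme at follow-up. For a given proportional drop in egg output, a lightly infected child reaches zero more easily than a heavily infected one. Baseline intensity should therefore carry information about who is cured. An unadjusted chi-square leaves that variation in the noise, and a chance difference in intensity between the arms stays in the estimated cure-rate difference.

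Two things are at stake: the width of the confidence interval for the ABZ-MBZ difference, and how the result can be defended if the arms turn out unequal in intensity. An adjustment chosen after seeing such an imbalance would be open to challenge as post hoc, whereas one fixed in advance would not.

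**Working it through.** **Inputs from the protocol.** Cure 75% (ABZ) and 51% (MBZ), alpha 5%, power 90%, 85 per arm (section 4.6), 1:1 allocation (4.8.1.4).

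**Inputs assumed.** SD of log10 baseline epg = 0.6. Odds ratio (OR) of cure per ten-fold higher epg: 1 (no association), 0.5, 0.3, 0.2, 0.1. The protocol gives none of these.

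**Step 1: the plan's own figure.** With mean rate 0.63,

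n = [z_α·√(2×0.63×0.37) + 1.2816·√(0.51×0.49 + 0.75×0.25)]² / 0.24²

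- Two-sided (z = 1.960): (1.338 + 0.848)²/0.0576 = 83, close to the stated 85.
- One-sided (z = 1.645), as section 4.6 says: (1.123 + 0.848)²/0.0576 = 68, which does not reproduce 85.

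**Step 2: power of the planned test at 85 per arm.** Two-sided: Φ[(0.24×√85 − 1.338)/0.661] = Φ(1.32) = 90.7%. One-sided: 95.0%. The planned test meets the 90% target either way.

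**Step 3: precision of the unadjusted difference.** SE = √[(0.2499 + 0.1875)/85] = 0.0717. The 95% half-width is 1.96×0.0717 = 14.1 percentage points.

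**Step 4: what adjustment adds.** Simulations at 85 per arm, with the overall cure rates held at 51% and 75%, compared the Pearson test with the likelihood-ratio test from a logistic model containing treatment and log baseline count. An OR per ten-fold converts to an OR per SD by raising it to the power 0.6 (for example 0.5^0.6 = 0.66, or 1.5 when inverted). The half-width is 14.1×√(1 − variance reduction).

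| OR per ten-fold epg | Inverted OR per SD | Variance reduction of risk difference | Half-width, points | Adjusted power (simulated) |
|---|---|---|---|---|
| 1 | 1 | 0% | 14.1 | 0.90-0.91 |
| 0.5 | 1.5 | 1-3% | 13.8-14.0 | 0.92 |
| 0.3 | 2.1 | about 9% | 13.4 | 0.93-0.94 |
| 0.2 | 2.6 | about 13% | 13.1 | 0.94 |
| 0.1 | 4.0 | 26-27% | 12.0-12.1 | 0.96-0.97 |

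Unadjusted simulated power was about 0.90-0.91 throughout. To reach 92%, 93.4%, 95% or 97%, the unadjusted test would need about 90, 95, 103 or 116 children per arm.

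**Step 5: do the gains carry over to the risk difference?** The simulated test is on the conditional log odds ratio, while the quantity of interest is the difference in cure rates. Using Φ(0.24/SE − 1.96) with SE = 0.0717×√(1 − reduction), reductions of 0%, 3%, 9%, 13% and 27% give 0.917, 0.925, 0.939, 0.948 and 0.975. The pattern is the same. The starting value is slightly above 0.907 because this formula uses the unpooled SE.

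**Step 6: type I error.** Under equal cure rates the simulated two-sided rates were 4.4-4.9% unadjusted and 4.7-5.4% adjusted.

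**Step 7: is the association plausible?** A Poisson egg-count model was built on the zero-egg definition of cure (assumed median of 10 or 40 eggs on four slides, SD of the natural log 1.0-1.5, varying spread of drug response). It gave inverted ORs of about 1.2 to 5.6 per SD and adjusted power of 90.5% to 97.4%. The direction is stable and the strength is not.

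**Step 8: chance imbalance.** The SD of the between-arm difference in mean log10 epg is 0.6×√(2/85) = 0.092. A 1.25-fold imbalance is log10(1.25) = 0.097, so its probability in either direction is 0.29. Its effect on the cure difference is at most |ln OR|×0.097×0.25, which is 1.7, 2.9 or 5.6 points for ORs of 0.5, 0.3 or 0.1. All are below one SE (7.2 points) and small beside the planned 24 points.

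**The case against.** The strongest case is that nothing here is wrong. Under randomisation the chi-square is a valid test of the cure-rate difference, and its error rate already allows for chance imbalance. The sample size delivers the promised power, and the 51% for MBZ was deliberately cautious. At the pooled rates quoted in section 4.6 (15% vs 75%), unadjusted power exceeds 99.9%. The SD and odds ratios are assumptions, and at the weak end the gain is one point of power or less. Covariate adjustment is also often left to an analysis plan, which may exist but is not shown.

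Most of this stands, and it rules out several stronger readings that a reader might draw:

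- That the result would be biased or the type I error inflated. Neither follows from section 4.9 under random allocation.
- That the trial is underpowered. Step 2 shows otherwise.
- That baseline intensity is an established strong predictor of cure. The protocol nowhere says so, and its definitions support only the direction.
- That adjustment would remove imbalance. It accounts only for the measured and correctly modelled part, and Kato-Katz counts are noisy.

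What does not stand is treating the point as mere missing detail. Section 4.9 names a specific unadjusted test as the between-group analysis. The point concerns that stated choice, and an analysis plan that made an adjusted analysis primary would depart from it.

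**Conclusion.** The point holds as a free improvement. The planned test is sound and adequately powered, but it ignores a covariate that is measured before allocation and is complete by design, since eligibility depends on it. The likely gain runs from nothing to about 6-7 points of power, and from 0% to about 27% of the variance of the risk difference (95% half-width from 14.1 down to about 12.0 points). In the middle of the assumed range the gain is 2-3 points of power. These sizes rest on 85 evaluable children per arm, cure rates of 51% and 75%, a log10 epg SD of 0.6, and an association whose strength the protocol does not give. In the simulations, adjustment cost nothing material when there was no association, which is why it is worth fixing in advance despite that uncertainty.

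**What to change.** In section 4.9, state that the primary comparison of cure rates is a logistic regression on treatment and log10 baseline hookworm epg. Report the standardised (marginal) difference in cure rates with a delta-method or bootstrap 95% CI, and a p-value for that same quantity so that test and interval agree. The conditional odds ratio should not be the headline, because it is a different quantity from the cure-rate difference. State whether the test is one- or two-sided and reconcile this with section 4.6, which says one-tailed while its 85 per group matches a two-sided calculation. Keep the unadjusted Pearson chi-square as a supporting analysis.

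The logarithm is always defined, because every randomised child has at least one egg at baseline. The cost is two or three sentences in the protocol and a short piece of code. No new data, visits or children are needed.
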